#### **8.4.1 Statistical Analysis**

A two-sided t-test will be used to compare cytokine differences between treatment groups as described above.

### **8.5 EGFRvIII CD4+ and CD8+ Cytokine Fluorescent Cytometry**

EGFRvIII-specific cellular immune responses will be monitored and evidence for the induction of autoimmunity will be sought. For cellular immune responses a polyfunctional analysis (Betts, Exley et al. 2005; Betts, Gray et al. 2006; Betts, Nason et al. 2006) of T-cell function will be performed as previously described (Betts, Exley et al. 2005). Briefly, cryopreserved PBMC samples are thawed and rested overnight at 37°C/5% CO2 in RPMI media containing 10% fetal calf serum (R10). The next day, the cells will be adjusted to 2x10^6/well and incubated with 1 µg/mL of each of the co-stimulatory MAbs αCD28 and αCD49d with or without peptide stimulation (2 µg/ml) in the presence of Brefeldin A (5 µg/ml Sigma-Aldrich, St. Louis, MO) monensin (1 µg/ml; Golgistop, BD Biosciences, San Diego, CA), and αCD107a-Alexa 680 for 5-6 hr at 37°C and 5% CO2. Following stimulation, cells will be treated with EDTA for 15 minutes at ambient temperature (AT, 18-22°C). The cells will be washed, and stained with MAbs specific for **CD4** (Cy5.5-PE), **CD8** Qdot 705, **CD45RO** PE-TR, **CD27** PE-Cy5, **CD57** Qdot 605, **CD14/CD19** (Cascade Blue) and a vital-dye reagent (LIVE/DEAD Fixable Violet Dead Cell Stain Kit for Flow Cytometry; Invitrogen Corp., CA) for 20 minutes at AT. After two washes, 1x BD FACS Lysing solution (BD Biosciences, San Jose, CA) will be added and samples will be incubated for 10 min at AT. After one wash, 1x BD FACS Permeabilizing Solution 2 (BD Biosciences, San Jose, CA) will be added and samples incubated for 10 minutes at AT. After one wash, cells will be stained with **αCD3** (Cy7-APC), **αIFN-γ** (FITC), **αTNF-α** (Cy7-PE), **αMIP1β** (PE), and **αIL2** (APC) for 30 minutes on ice, washed, and fixed in PBS containing 1% formaldehyde (Sigma-Aldrich, St. Louis, MO). In all experiments, a negative control (αCD28/49d), and a positive control (SEB, 10 µg/ml, Sigma-Aldrich) will be included. The samples are acquired on a custom LSRII polychromatic flow cytometer (BD Immunocytometry System, San Jose, CA) equipped for detection of 17 fluorescent parameters. We are planning to collect a minimum of 500,000 total lymphocytes from each sample, because we expect the frequency of responding cells to be between 0.05 and 1.0%. This number of events is required based on calculations performed by [name] (BD Bioscience, personal communication) to detect a statistically significant number of positive events that can be used for the analysis of the data and the characterization of the different populations. Antigens used in this assay will include PEPvIII, KLH, CEF peptide mix, total tumor lysate, and autologous normal brain lysate. Ideally, we would be able to select a validated surrogate immunologic response marker for clinical efficacy, but no such marker has been identified to date and studies to validate such a marker

would need to be large and prospective and would be clearly beyond the scope of this proposal. It would be our intent, however, to incorporate any additional knowledge that becomes available at the time of data analysis to evaluate the relative biologic significance of the immune response markers that we have chosen.

### **8.5.1 Statistical Analysis**

The analysis used here will be one that has been successful at distinguishing HIV progressors and non-progressors based on T-cell phenotype (Betts, Exley et al. 2005; Betts, Gray et al. 2006; Betts, Nason et al. 2006). All data will be background subtracted. For each measure, a lower threshold corresponding to 2SD above background is set to 0 based on a Poisson model essentially allowing T-cells to be designated as positive or negative for a certain phenotypic marker. The number of positive phenotypic markers post-vaccination will be calculated for each patient. Treatment groups (+/- daclizumab) will be compared relative to the number of phenotypic markers observed post-vaccination for each antigen using a Wilcoxon rank sum test. Additional exploratory analyses will be conducted using a Fisher's exact test that will compare treatment groups with respect to the proportion of patients with  $\geq 4$  positive markers. Correlations between phenotypic markers and EGFRvIII loss on recurrence will also be sought.

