## 2 HYPOTHESES AND OBJECTIVES

### 2.1 Hypotheses

- Our primary hypothesis is that:
  - Daclizumab will inhibit the functional and quantitative recovery of TRegs in patients with newly-diagnosed high grade glioma during homeostatic proliferation after therapeutic TMZ-induced lymphopenia.
- Secondary hypotheses that will be explored in this study are that:
  - Daclizumab will be safe in combination with CDX-110 in patients with newly-diagnosed high grade glioma during recovery from TMZ-induced lymphopenia.
  - The magnitude and character of humoral and cellular CD8+ and CD4+, EGFRvIII-specific T cell responses will be enhanced in adult patients with newly-diagnosed high grade glioma treated during recovery from TMZ-induced lymphopenia when daclizumab is given during the T cell recovery phase.
  - Daclizumab will not enhance antigen-specific or generalized activation-induced cell death or induce immunologic or clinical evidence of autoimmunity.
  - Daclizumab will alter the phenotype (CD56-expression), cytokine secretion profile, or cytotoxicity of CD3-CD56+ NK cells.
  - Treatment of adult patients with newly-diagnosed high grade glioma using CDX-110 during recovery from TMZ-induced lymphopenia with or without daclizumab will ultimately produce evidence of a prolonged time to progression (TTP) and overall increase in median survival in these patients compared to a matched historical cohort from MD Anderson Cancer Center (provided by [name]).

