### **2.2.2      Secondary Objectives**

- To evaluate the safety of daclizumab in the context of vaccinating adult patients with newly-diagnosed high grade gliomas using CDX-110 during recovery from therapeutic TMZ-induced lymphopenia.
- To determine if daclizumab enhances the magnitude or character of CDX-110-induced cellular or humoral immune responses, inhibits or enhances activation-induced cell death, or induces immunologic or clinical evidence of autoimmunity.
- To determine if daclizumab alters the phenotype (CD56-expression), cytokine secretion profile, or cytotoxicity of CD3-CD56+ NK cells.
- To determine if daclizumab in addition to vaccination extends progression free survival compared to historical cohorts.
- To characterize immunologic cell infiltrate in recurrent tumors and seek evidence of antigen escape outgrowth.

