### **8.1.1 Overview of Statistical Analysis**

Our laboratory and the HVTN Immunologic Monitoring Reference Laboratory, headed by [name] also at Duke University, has devoted considerable effort to co-developing and co-validating the immunologic assays outlined below for monitoring  $T_{Reg}$  function, antigen-specific responses in CD8+ or CD4+ T-cells, and NK cell functional activity in cancer patients. The reproducibility of these assays in our hands ensures that they can be reliably used for monitoring of changes after vaccination with and without daclizumab. Power calculations for this study are based on our primary endpoint which is functional suppressive capacity of CD4+CD25+CD127-  $T_{Regs}$ . For these calculations, we assumed that measurements made in each treatment group at a given phytohemagglutinin (PHA) level would be normally distributed with standard deviation of  $\sigma$ . Based on our experience with these assays within this patient population (Fecci, Mitchell et al. 2006), we estimate that with a sample size of 20 randomized patients we will have 80% power to detect a difference of 1.41  $\sigma$  at the 0.017 significance level (one-tailed). A 0.017 level of significance is used to adjust (Bonferroni correction) for the use of 3 non-zero PHA doses (0.1, 1, 10  $\mu$ g/well) in the proliferation assay. Thus, with only 20 patients, we will have sufficient power to detect treatment effects much more subtle than the ones observed in our pre-clinical studies (Fecci, Sweeney et al. 2006) and effects that we believe would be clinically significant. However, because the magnitude and variability of the effects of daclizumab on  $T_{Regs}$  remain unknown in humans, once human data become available from these studies, power analyses will be recalculated and patient numbers adjusted if needed. If daclizumab treatment does not significantly inhibit the functional recovery of  $T_{Regs}$  (primary endpoint), we would not be interested in the further development of this drug as

a vaccine adjuvant. Therefore, a one-sided hypothesis test is utilized. Power calculations are not provided for subsequent analyses as the number of patients in this trial will be determined by the primary endpoint, and the remainder of the analyses is exploratory and hypothesis generating only. With 10 patients in each arm, however, we will have 80% power to detect difference  $>1.325\sigma$  between groups for each assay at  $\alpha=0.05$ .

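### Section 8.5.1 compares the arms only on a count of positive markers, so the frequency of EGFRvIII-specific T cells is not compared and the count is likely to be insensitive to a larger response

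*Protocol*

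**What the plan says.** Section 8.5 describes a multi-colour cytometry assay of EGFRvIII-specific CD4+ and CD8+ responses. On yield it says "We are planning to collect a minimum of 500,000 total lymphocytes from each sample", and gives the reason: "we expect the frequency of responding cells to be between 0.05 and 1.0" per cent.

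Section 8.5.1 subtracts background and applies a cut: "a lower threshold corresponding to 2SD above background is set to 0 based on a Poisson model". I read this as setting anything at or below the cut to zero, so that each marker is positive or negative. Then "The number of positive phenotypic markers post-vaccination will be calculated for each patient". The arms are compared on this count for each antigen by a Wilcoxon rank sum test, and on the proportion of patients with four or more positive markers by Fisher's exact test. No other between-arm comparison is given for this assay.

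The hypothesis it serves is in section 2.1: "The magnitude and character of humoral and cellular CD8+ and CD4+, EGFRvIII-specific T cell responses will be enhanced". The matching objective in section 2.2.2 is looser: "To determine if daclizumab enhances the magnitude or character of CDX-110-induced cellular or humoral immune responses". Section 8.1.1 adds a remark on sensitivity: "With 10 patients in each arm, however, we will have 80% power to detect difference" of more than 1.325σ for each assay at α = 0.05. The same section calls everything beyond the primary endpoint exploratory.

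**The concern.** The assay already yields a quantitative result, the background-subtracted frequency of responding cells. Section 8.5.1 reduces it to yes or no per marker and tests only the number of yeses. If the cut lies far below the usual response, a patient who responds at all is positive on most markers. Both arms receive the vaccine, so responders in both arms would cluster at the top of the scale. A response several times larger under daclizumab would then leave the count unchanged.

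At stake is the reading of a secondary result. The count can show whether more patients respond, but hardly whether they respond more strongly, and section 2.1 hypothesises the latter as well. Section 8 says the immunologic tests will help to design later trials, so a null result produced by a ceiling could mislead.

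**Working it through.** **The plan's own figure.** For 10 per arm and a difference of 1.325 SD, the noncentral t distribution gives power 0.800 at two-sided α = 0.05. The 80% reproduces, as a statement about a t-test on a continuous measure.

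**Where the cut lies.** Inputs from section 8.5: N = 500,000 events and 0.05–1.0% responding cells. Background is not given; I assume 0.01–0.2%.

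- Lowest expected response: 0.0005 × 500,000 = 250 events.
- Cut above background: 2√(N × background).
- Background 0.01% (50 events): 2√50 = 14.1 events = 0.0028%.
- Background 0.2% (1,000 events): 2√1,000 = 63.2 events = 0.0126%.
- The lowest expected response is therefore 250/63.2 = 4.0 to 250/14.1 = 17.7 times the cut.
- For 250 events to equal the cut, background would have to be (250/2)² = 15,625 events, or 3.1%.

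**In SD units.** Assume log-normal frequencies whose central 95% is 0.05–1.0%.

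- Centre: √(0.05 × 1.0) = 0.224%.
- Log SD: ln(1.0/0.05)/3.92 = 0.764.
- The cut is ln(0.224/0.0126)/0.764 = 3.8 to ln(0.224/0.0028)/0.764 = 5.7 SD below the centre.
- A shift of 1.325 SD is exp(1.325 × 0.764) = 2.75-fold.

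**Power of the count.** Simulation with 10 per arm, five markers, correlation 0.7, a shift of 1.325 SD and two-sided α = 0.05. Ranges cover 500,000 events with background 0.01–0.2% and 100,000 events with background 0.01–0.05%; the last row has background 0.01–0.05% only. Frequency means the average over the five markers.

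| Each marker's frequency relative to 0.05–1.0% | Wilcoxon on count | Wilcoxon on frequency |
|---|---|---|
| Same | about 0% | 84–90% |
| One fifth | 0–59% | 84–87% |
| One twentieth | 15–74% | 72–88% |
| One fiftieth | 35–70% | 43–81% |

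In the first row 97–100% of control patients score the maximum. Ranges in the lower rows overlap, but within each setting the frequency test was ahead. The Fisher test on four or more markers has 0% in the first row and about 40% at most elsewhere.

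**Without assuming a background.** The cut can instead be placed directly (correlation 0.5–0.8). Power of the count is 59–75% with the cut 0.5 SD below the saline-arm mean, 30–51% at 1 SD, 5–13% at 1.5 SD and 1% or less at 2 SD. A Wilcoxon test on one marker's frequency has 75–76%, and on the mean of five log frequencies 83–93%. Part of the gain thus comes from combining functions.

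**Non-responders.** Section 3.4.3 reports 62% skin-test reactivity and 38% five-fold antibody responses in the earlier trial; I use these only as assumed responder fractions.

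- Equal fractions in both arms, with a 1.325 SD larger response among daclizumab responders: count 4–5%, frequency 6–19%.
- 38% against 80% responders: count 44%, frequency 72%.

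**The case against.** Several points on the other side stand.

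- **Magnitude is tested elsewhere.** A reader might infer that the magnitude objective is never tested. That is not so. The objective reads magnitude or character, cellular or humoral. Sections 8.4.1, 8.6.1, 8.8.1 and 8.9.1 apply t-tests to cytokine production, proliferation and cell-death markers, antigen-stimulated proliferation and secretion, and antibody concentration. What they do not give is the frequency of EGFRvIII-specific CD4+ and CD8+ cells. Section 10.3.1 uses EGFRvIII-specific IFN-γ-producing CD8+ cells only as a predictor of progression or survival.
- **The scale is not defined.** A maximum of five is an inference from the five functional stains (CD107a, IFN-γ, TNF-α, MIP1β, IL-2). CD45RO, CD27 and CD57 are stained too, and section 8.5.1 does not list which markers count.
- **Saturation is conditional.** The 0.05–1.0% refers to responding cells, not to each marker, and 500,000 refers to all lymphocytes, not to a gated subset. With 50,000 gated events and 0.2% background, the cut is 2√100 = 20 events, or 0.04%, only 1.2 times below 0.05%. Non-responders would not sit at the top.
- **The 80% is not a promise about this count.** Section 8.1.1 disclaims power for the later analyses, and section 8.5.1 states none. Still, its remark about each assay should not be read as covering the marker count.
- **A count is a fair measure of character**, and the analysis is declared exploratory.

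None of this supplies a between-arm comparison of frequency in this assay, and the rule in section 8.5.1 is written out rather than left open.

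**Conclusion.** The point holds in a limited form. Section 8.5.1 plans no between-arm comparison of the frequency of EGFRvIII-specific T cells, although section 2.1 hypothesises that magnitude as well as character is enhanced. Taken at the protocol's own frequency and event number, the cut lies well below expected responses and the count is likely to sit near its maximum in responders of both arms. Power for a 1.325 SD shift is then about 0% for the count against 84–90% for frequency.

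That size rests on assumed background, five markers, their correlation, and each marker being as frequent as responding cells overall. Under less favourable inputs the loss falls to a modest one. It would go too far to say that a real enhancement will be reported as no difference: that is one scenario, and if the arms differ in responder fraction the count keeps some power. Nor does the frequency test rescue everything. With equal responder fractions and many non-responders, both tests are weak. The consequence is confined to one exploratory assay.

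**What to change.** In section 8.5.1:

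1. Make the main between-arm comparison for each antigen a Wilcoxon rank sum test on the background-subtracted frequency of antigen-specific CD4+ and CD8+ cells. Use one combined frequency per subset (total responding cells, or the mean log frequency over the functions) rather than a separate test per function.
2. Name the markers that enter the count, which fixes its maximum.
3. Keep the marker count and the proportion with four or more as supportive measures of character.

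The cost is a few sentences and a few more exploratory comparisons. No new samples or assays are needed, because the frequencies are already produced.

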## **8.6 Activation-induced Cell Death and *In Vivo* Proliferation**

The frequency of proliferating versus apoptotic cells will be determined by intracellular expression of the proliferation marker Ki67 or active Caspase 3 in T-cell subsets, respectively. Freshly isolated PBMC cells (Sigma Accuspin tubes) or PBMC pulsed with PEPvIII-KLH or antigens of interest are stained for surface expression with anti-CD3/CD4/CD8/CD25 (commercially available from BD), washed in 1X PBS containing 1% BSA and 0.1% NaN3 (PBS Wash) and red cell depleted with BD Lyse. Samples are then washed and fixed with FACS permeabilizing solution (Becton Dickinson), incubated with saturating amounts of anti-Ki67-FITC (Beckman-Coulter) and anti-active Caspase 3 (BD Pharmingen) (30 mins @ 4°C), and then washed and resuspended in 0.5mL PBS Wash with 0.4% paraformaldehyde. Multi-color flow cytometric acquisition/analysis of the samples will be performed on a BD LSRII flow cytometer (Becton Dickinson) in the Duke Human Vaccine Institute Flow Cytometry Facility. This LSRII instrument has two lasers (488nm, 633nm) and 7 fluorescent channels and 2 scatter channels. We routinely run similar 4-7 color panels on mouse, rhesus, and human cells to assess proliferation status in specific cell subsets (Sempowski, Hicks et al. 2005).

### **8.6.1 Statistical Analysis**

All data will be background subtracted and compared between treatment groups using unpaired t-tests as described above..

## **8.7 Delayed-type Hypersensitivity**

To assess for patients' baseline and progressive status of cellular immunity, routine skin tests will be performed before the first immunization, and at the time of the fourth

vaccination. Patients will receive DTH skin test to the common recall antigens *Trichophyton*, *Candida* and Tetanus in order to try and assess immunocompetence.

### **8.7.1 Statistical Analysis**

Assuming that all patients will have no response before vaccination, each patient will be classified as a responder or non-responder based upon an induration at the response site  $\geq 10$  mm. Fisher's exact test will be used to compare responses between groups after each vaccination.

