### **5.2.3 DTH Placement and Biopsy Procedure**

After completing RT and along with vaccination #1 patients will undergo baseline DTH testing with standard recall antigens. The vaccine site will also be assessed for a DTH-type response. Recall antigens (Tetanus toxoid, *Candida*, and *Trichophyton*) will be prepared and administered according to SOP-JHS-HDC-CL-014 “Delayed type hypersensitivity testing and biopsy procedure”. Beginning at the time of the fourth vaccination, the DTH tests for recall antigens will be repeated. An additional leukapheresis will be required for any patients who have a positive DTH skin test for PEPvIII for immunologic monitoring. The patient will be monitored after the administration of all skin tests for the development of severe allergic reactions. A physician or nurse who has completed an ACLS course will supervise the skin tests, and a cardiac resuscitation cart will be available in the immediate vicinity when performing these procedures. A 5 mm diameter of erythema or induration will be considered positive. Patients with positive reactions at the site of human PEPvIII-KLH will be biopsied under local anesthesia for evaluation of the infiltrate (SOP-JHS-014 “Delayed Type Hypersensitivity Testing and Biopsy Procedure”). The biopsy will be a standard 4 mm “punch” biopsy routinely used in the Dermatology Clinic.

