### **6.2.4 During and After Immunizations**

- Clinical evaluations with each vaccine or leukapheresis will include a general physical, neurologic, and ophthalmologic examination, KPS, and MMSE.
- Radiographic evaluations consisting of a contrast enhanced brain CT or MRI scan will be obtained every 8  $\pm$  4 weeks.
- Blood will be obtained for T4/T8 ratio (Lab Code 2500202), ABC (Lab Code 2010200) with manual differential (Lab Code 2000640), serum for PEPvIII-KLH ELISA ([name] Lab), and 10 yellow ACD (9 mL), 3 red (9 mL), and 1 purple (3 mL) tubes for Immunologic Monitoring *prior* to vaccination #1 and with each vaccination after vaccination #3. Blood will also be obtained for

sub-clinical autoimmunity prior to vaccine # 1 and every 4 months after vaccine # 3. Estimated volume of blood for these tests is 120 cc.

- During TMZ cycles, ABC (Lab Code 2010200) with manual differential (Lab Code 2000640) will be monitored at the time of vaccination (day  $21 \pm 2$ ) and before the next TMZ dosing of each 4 week cycle.
- DTH testing will occur with the fourth vaccination (SOP-JHS-HDC-CL-014 “Delayed Type Hypersensitivity Testing Procedure”). Results will be read and recorded on the appropriate form (FORM-JHS-HDC-CL-014C “Delayed Type Hypersensitivity Testing Form”)  $48 \pm 24$  hours later. An additional leukapheresis will be required for any patients who have a positive DTH skin test for PEPvIII for immunologic monitoring.

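### The DTH responder rule assumes a nil baseline, although the section tests recall antigens and measures them before vaccination; the arm comparison is diluted, not biased

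*Protocol*

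**What the plan says.** Section 8.7 schedules skin tests before the first immunization and at the fourth vaccination: "Patients will receive DTH skin test to the common recall antigens" Trichophyton, Candida and Tetanus, "in order to try and assess immunocompetence". Section 5.2.3 also calls for baseline testing with recall antigens and adds that the vaccine site will be read for a DTH-type response.

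Section 8.7.1 then starts from "Assuming that all patients will have no response before vaccination". On that footing "each patient will be classified as a responder or non-responder based upon an induration at the response site" of 10 mm or more, and Fisher's "exact test will be used to compare responses between groups after each vaccination". The rule does not use the baseline reading, does not name the antigen or site, and does not say how to treat a patient who was positive beforehand.

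Section 5.2.3 defines positivity differently: "A 5 mm diameter of erythema or induration will be considered positive". On timing, section 6.2.4 says "DTH testing will occur with the fourth vaccination".

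**The concern.** A recall antigen probes memory that the patient may already have, so a positive baseline is an ordinary result. Section 8.7 measures that baseline and section 8.7.1 assumes it away. A patient with 10 mm to Candida before vaccination and 10 mm afterwards is a responder under the rule, although nothing changed.

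Two things are at stake. Responder rates within each arm would include reactivity that predates treatment. The difference between arms would also shrink, because only patients negative at baseline can show an effect. In addition, the comparison is planned at times, and with a cut-off, that other sections do not share.

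**Working it through.** **Plan's own figure.** The protocol gives no power, response rate or sample size for the DTH comparison, so there is nothing to reproduce.

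**Inputs from the protocol.**
- 10 patients per arm (section 8.1.1).
- Significance level 0.05 for this and the other assays (section 8.2.1).
- Fisher's exact test on a 10 mm responder rule (section 8.7.1).

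**Assumed inputs.**
- b, the share of patients already at or above 10 mm at baseline, taken as 0 to 70%.
- p, the true conversion rate among baseline non-responders, taken as 10% on saline and 60% on daclizumab.
- A patient positive at baseline stays positive.

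**Formula.** The observed responder rate in an arm is b + (1 − b) × p, and the observed difference is (1 − b) × (0.60 − 0.10). At b = 30%:
- saline: 0.30 + 0.70 × 0.10 = 0.37
- daclizumab: 0.30 + 0.70 × 0.60 = 0.72
- difference: 0.35, against a true conversion difference of 0.50
- share of responders already positive before vaccination: 0.30/0.37 = 81% on saline and 0.30/0.72 = 42% on daclizumab

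**Power.** This is the exact two-sided Fisher test, enumerated over binomial outcomes. The last column restricts the test to baseline-negative patients and averages over how many there are in each arm.

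| b | Observed rates | Difference | Rule as written | Conversion among baseline-negatives |
|---|---|---|---|---|
| 0 | 10% vs 60% | 50 points | 0.474 | 0.474 |
| 30% | 37% vs 72% | 35 points | 0.177 | 0.354 |
| 50% | 55% vs 80% | 25 points | 0.090 | 0.196 |
| 70% | 73% vs 88% | 15 points | 0.031 | 0.055 |

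**No effect at all.** If nobody converts in either arm, the rule still reports on average 10 × b responders per arm: 3 at b = 30% and 5 at b = 50%. The chance of a significant difference between arms is 0.012 and 0.013 respectively, well below 0.05.

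**Passages side by side.**

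| Item | One place | Another place |
|---|---|---|
| Positive test | 5 mm, erythema or induration (5.2.3) | 10 mm induration (8.7.1) |
| Reading window | 48 ± 24 hours (6.2.4) | 48–72 hours (flow sheet footnote 22) |
| Baseline test | With vaccine #1 (5.2.3) | Pre-temozolomide leukapheresis, with no mark at immunization #1 (flow sheet) |
| Later tests | After each vaccination (8.7.1); vaccine #4 (8.7, 6.2.4) | Immunizations #3 and #4 and progression (flow sheet) |

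**The case against.** The strongest defence is that the response site in 8.7.1 means the PEPvIII or vaccine site. The assumption would then have support: section 3.4.3 reports that the earlier vaccine trial saw no baseline DTH response to the vaccine components. A comparison after each vaccination would also make more sense, since section 5.2.3 has the vaccine site read. But 8.7.1 does not say this, and its parent section names recall antigens only. If that reading was intended, the text still has to say so, and the recall tests are left without a stated analysis.

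A related objection carries weight. The secondary objective concerns responses induced by CDX-110, whereas the recall tests are there to gauge immunocompetence. If the rule applies to recall antigens, its bearing on that objective is limited. Section 8.1.1 also declares every analysis beyond the primary endpoint exploratory, and 8.7.1 attaches no decision to DTH.

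The baseline and conversion rates above are assumed. The protocol describes impaired T-cell immunity in these patients (section 3.9), so the 50% and 70% rows may be too high. Even with no baseline responders, the assumed effect has only 47% power.

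**Conclusion.** The point holds. For recall antigens, 8.7.1 fixes a responder rule on an assumption that the trial's own test panel does not support, and it ignores a baseline that the trial measures. The consequence is inflated responder rates in both arms and a diluted comparison. Under the stated assumptions, power falls from 0.47 to 0.18 at 30% baseline positivity and to 0.09 at 50%. Counting conversion among baseline-negatives gives about double those last two values.

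Three stronger inferences are not supported.
- **Bias toward daclizumab.** Both arms are vaccinated and allocation is random, so baseline responders are expected equally in each. The between-arm error rate stays below 0.05.
- **A large power gain from correcting the baseline alone.** In a simulation with an assumed baseline SD of 5 mm, change SD of 4 mm and shift of 5 mm, the 10 mm rule had about 8–12% power and a change score about 72–76%. Counting only new positives, which corrects the baseline but keeps the dichotomy, gave about 5–15%. Most of that gap therefore comes from dichotomizing.
- **Vaccine #4 as the only later test.** The flow sheet also marks DTH at immunization #3 and at progression, so the schedule itself is in conflict.

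This is an exploratory secondary endpoint, and severity is low to moderate.

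**What to change.** In section 8.7.1:
1. Name the antigen or site that each analysis uses.
2. Delete the no-response assumption for recall antigens. For these, compare arms on the change in induration from the measured baseline, per antigen and adjusted for baseline. Report conversion from negative to positive as supportive.
3. Keep a responder rule with an assumed nil baseline, if at all, only for the PEPvIII or vaccine site, and cite the earlier trial as its basis.

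Across sections 5.2.3, 6.2.4, 8.7, 8.7.1 and the flow sheet, reconcile the positive cut-off, the reading window, the baseline time point and the post-baseline time points. Then replace "compare responses between groups after each vaccination" with the agreed times.

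The analysis change is wording only, because a baseline test is already scheduled. The schedule needs an actual decision first: a reading before radiation and temozolomide and one taken with vaccine #1 are different baselines.
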